**Figure 4 figure4:**
[figure not shown]
Pre and Posttest Process of development of EDDy.

#### Analysis

Study participants will be followed up for 6 months and will be analyzed primarily for their adherence to using EDDy. It will be assessed based on patients’ willingness to use it, the ease of use, their acceptance of EDDy in terms of the contextual relevance, and the clinical utility. The participants will undergo an exit survey at the end of the study period using a validated questionnaire. It will be specific for assessing the qualitative parameters such as *user experience*, *glycemic control*, *adherence leading to improvement in their SMBG*, and *clinical utility.*

The qualitative outcomes are as follows:

Ease of use and adherence: User’s perception on accessing the various modules in the app, ease of entering information, ease for retrieving information, and ease of comprehending informationGlycemic control: Adherence in terms of regular monitoring and tracking of blood glucose values to keeps it under check, leading to well-managed T2DMContextual relevance: Relevance of the contents of EDDy in terms of the user expectations and requirements as expressed in phase 1 of the studyAdherence to SMBG and DSM practices: Reminders and alerts that ensure adherence to medications, insulin injections, regular glucose testing, and comorbidity screeningClinical utility: Improvement in treatment outcomes due to adherence to reminders or alerts and monitoring of blood glucose, adherence to medication, and follow-ups

The frequency will be tested based on the Diabetes Co-Conditions Screening Checklist provided by the Association of Diabetes Care & Education Specialists [11].

The following standard tools will be used for assessment, which are modified according to the study requirements and will be content validated by experts:

Perceived Health Web Site Usability Questionnaire: A 12-item questionnaire that is validated for assessing the usability of health websites for older adults will be used [12].Diabetes Self-Management Questionnaire: It describes self-care activities related to diabetes. SMBG practices will be analyzed using this tool. A validated 12-item questionnaire to assess self-care activities associated with glycemic control will be used [13].A self-developed, content-validated questionnaire: Adherence will be evaluated, including the regularity of use; ease of use with respect to entering diabetes-related information such as regular testing and entry of glucose levels; adherence to medications or insulin doses; reporting of diabetes-related emergencies or complications, if any; and adherence to periodic screening such as laboratory investigations, peripheral neuropathies, retinopathy, diabetic foot, and BMI.

The physicians will be interviewed to assess the clinical utility of the app and their experience in using the app using a content-validated questionnaire.

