#### Study Design

Phase 3 will involve testing the adherence and usability of the developed app. This phase will use a pre- and posttest design among 48 patients with diabetes selected through purposive sampling.

At a 5% level of significance with 80% power and an effect size of 0.25, the minimum sample size required for a single-group, repeated measures study design involving 1 primary quantitative outcome (adherence) measured across 3 time points (preintervention, after 3 months, and after 6 months; correlation among repeated measures is 0.3) to understand the adherence to EDDy integrated with an HIS is 38 individuals. Incorporating a dropout rate of 20%, the minimum sample size requirement is 48 individuals.

The sample size was computed using G*Power (version 3.1.9; Universität Düsseldorf). The sample size may be amended (if required) based on pilot study findings.

The study setting will be the endocrinology OPD of a tertiary care hospital in coastal Karnataka, India.

Regarding study participants, patients with T2DM who have regular follow-up records will be considered for the study.

This study will analyze the adherence of patients with T2DM to EDDy in comparison to the existing manual method of documentation. Adherence will be evaluated in terms of the following:

Adherence of entering SMBG values as predetermined by the patient: The study participants will be instructed to fix the frequency that they will monitor their blood glucose; based on this frequency, they will be prompted to conduct the glucometer testing and enter the values into EDDy. The values will be stored in the app and will be transferred to the server on a regular basis as the EDDy is integrated with an HIS.Adherence to diabetes self-management (DSM) practices: Pre- and posttest adherence to DSM practices will be analyzed using the same content-validated questionnaire.Adherence to routine blood investigations and screening regimen: Pre- and posttest adherence to periodic blood investigation and comorbidity screening will be analyzed.

The inclusion and exclusion criteria for sample collection will remain same as that of phase 1.

Phase 3 will be evaluated in 3 intervals:

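### The sample size rests on one quantitative adherence outcome measured three times, but the article never identifies that variable, and its Analysis section describes primary adherence through perceptions instead

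*Protocol article*

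**What the plan says.** All places are in the Protocol article, Methods, Phase 3.

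- **Study Design, sample size.** The calculation is for a "single-group, repeated measures study design" with "1 primary quantitative outcome (adherence) measured across 3 time points" (preintervention, 3 months, 6 months). It gives 38 patients, or 48 after 20% dropout.
- **Study Design, components.** "Adherence will be evaluated in terms of the following" introduces three items: entering glucose values in the app at the frequency the patient has set; self-management practices, by questionnaire, before and after; and uptake of blood tests and comorbidity screening, before and after. The article gives no combining rule and no lead item.
- **Study Design, evaluations.** A questionnaire on current practice is given at enrolment and repeated at the third evaluation. A follow-up is planned in month 3, but no instrument is named for it.
- **Analysis, opening paragraph.** The primary analysis target is adherence to using the app, assessed through "willingness to use it, the ease of use, their acceptance of EDDy in terms of the contextual relevance, and the clinical utility". The list of qualitative outcomes that follows includes ease of use together with adherence, described as user perception.
- **Analysis, tools.** For the self-developed questionnaire: "Adherence will be evaluated, including the regularity of use; ease of use with respect to entering diabetes-related information". It also covers medication, reporting of emergencies and periodic screening.

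**The concern.** A sample size for one quantitative outcome has meaning only if the reader can tell which variable carries the assumed effect size and correlation. Here the variable could be app entries, a self-management score, screening uptake, a mixed questionnaire or a set of perceptions.

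The perception description is the most serious. A patient may find the app easy and relevant and enter nothing, or find it awkward and enter every reading. If the Analysis text is followed literally, the primary result answers whether patients like the app and not whether they adhere to it.

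The study has no control group, so fixing the primary outcome in advance is one of its main protections against selective reporting. With several unranked candidates, whichever one moves could be presented as the primary result.

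**Working it through.** **1. Reproduce the stated sample size.**

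Inputs from Study Design: "At a 5% level of significance with 80% power and an effect size of 0.25", three time points, and "correlation among repeated measures is 0.3". The effect size is read as Cohen's f, as G*Power uses it for repeated-measures ANOVA within factors. One group and sphericity (epsilon = 1) are assumed.

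- Noncentrality: lambda = f² × N × m / (1 − rho) = 0.0625 × 38 × 3 / 0.7 = 10.18.
- Degrees of freedom: m − 1 = 2 and (N − 1)(m − 1) = 74.
- Power from the noncentral F at 5%: 0.806 at N = 38 and 0.794 at N = 37, so 38 is the minimum.
- Dropout: 38 / 0.8 = 47.5, rounded up to 48.

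Both stated figures reproduce.

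**2. Set each candidate against what the calculation needs.** It needs one quantity, on a numerical scale, taken at all three visits, including the visit before the app is installed.

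| Candidate | Before the app | Month 3 | Month 6 |
|---|---|---|---|
| Entry of glucose values in the app | cannot exist | possible | possible |
| Self-management questionnaire | yes | not stated | yes |
| Blood test and screening uptake | yes | not stated | yes |
| Willingness, ease of use, relevance, utility of the app | cannot exist | not stated | exit survey |
| Self-developed questionnaire | only the items not about the app | not stated | not stated for this tool by name |

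No row is clearly filled in all three columns.

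**3. Scenarios.** The article does not say that any of these will be done. They show how much depends on the missing definition. Each assumes f = 0.25 and rho = 0.3 for every measure.

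- *Three Study Design components, each tested at 5%, success on any one.* With independent tests the family-wise error is 1 − 0.95³ = 0.143. With positive correlation it lies between 5% and 14.3%.
- *The same three with Bonferroni.* The level is 0.05 / 3 = 0.0167, and power per component at N = 38 is 0.660. For 80% per component, 49 evaluable are needed; 49 / 0.8 = 61.25, so 62 enrolled.
- *An outcome measured only before and after.* With m = 2, lambda = 0.0625 × 38 × 2 / 0.7 = 6.79 on 1 and 37 degrees of freedom, and power is 0.718. For 80%, 46 evaluable are needed; 46 / 0.8 = 57.5, so 58 enrolled.

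The last result depends on holding f at 0.25. If the means instead change linearly over three visits with f = 0.25, the first-to-last difference is 2 × 0.25 / √(2/3) = 0.612 SD. The standardised paired difference is then 0.612 / √(2 × 0.7) = 0.518, and a paired test on 38 patients has power 0.874. The two-point power therefore depends on the assumed pattern of change and need not fall below 80%.

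**The case against.** The best defence is that Study Design lists domains and the tools list names instruments. The self-developed questionnaire covers glucose testing and entry and periodic screening, which largely match the Study Design components, so the two may be one construct and its instrument. This stands. A reader might infer three mutually incompatible definitions, but the text supports only that these two are not reconciled, and that the questionnaire also mixes in ease of use. The firm conflict is between both of them and the opening of Analysis.

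That opening may itself be loose drafting. The Methods Overview names adherence, usability, contextual relevance and clinical utility side by side; usability has its own 12-item tool; and physicians are interviewed on clinical utility. This suggests the authors know the difference, but the sentence describing the primary assessment still says otherwise.

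A reader might also infer that the 5% level and 80% power are already lost. The documents do not support that. Nowhere does the article say that each component is tested at 5% or that one success is enough, and a single prespecified score would leave 38/48 intact.

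Nor does it follow that self-reported regularity of use merely duplicates the server record. The server holds nothing before installation, so a baseline must come from another source.

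Finally, how a score is built can be left to a full protocol or analysis plan. But an unseen document does not remove a conflict in the published text about what the primary outcome is.

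**Conclusion.** The point holds in this form: the article sizes Phase 3 on one quantitative adherence outcome at three visits, does not identify it, and in Analysis assesses primary adherence through perceptions that do not measure it. The calculation is correct (power 0.806 at 38; 48 enrolled) but has no defined variable to apply to.

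The multiplicity range (5% to 14.3%), the Bonferroni power (66.0%) and the two-point power (about 72%) are scenarios. They rest on the same f and rho for every measure. The upper error bound also requires independence, which is unlikely for measures taken on the same patients. They are not properties of the plan as written.

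**What to change.** 1. **Study Design, sample size.** Name one quantitative adherence score that exists before the app and can be measured the same way at all three visits, and state that 38/48 refers to it alone. One option is the proportion of planned glucose readings that are documented, from the paper record at baseline and from the app afterwards. Another is one named questionnaire score. The total of the self-management questionnaire is a weaker choice, because the stated target is adherence to the app and not self-care in general.
2. **Study Design, components.** Make the remaining components secondary. If more than one is to stay primary, state the multiplicity rule and recompute the sample size.
3. **Study Design, evaluations.** State that the chosen score is collected at month 3, or restate the power for two time points with the effect size justified for that contrast.
4. **Analysis.** Take willingness, ease of use, contextual relevance and clinical utility out of the description of adherence and report them as acceptability, usability and utility outcomes. Remove the primary outcome from the qualitative list.

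**Cost.** The other adherence components become secondary. The instrument may need one added administration at the month-3 follow-up that is already planned. If documented readings are chosen, the planned number at baseline and the handling of patients without a paper record must be defined; in the pilot 28 of 50 did not document their values. By the article's Study Status section, Phase 3 comes after app development, so these changes can be made before enrolment.

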**Objective:**

The objectives of the study are (1) to develop the HIS-integrated Electronic Diabetes Diary (EDDy) per the end-user expectations at a tertiary care hospital in a south Indian state with a high prevalence of T2DM and (2) to evaluate and test adherence to EDDy in the management of T2DM.

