**Methods:**

The study will be carried out in 3 phases. Phase 1 involved in-depth interviews with primary end users to gather information regarding their expectations from the hospital-based EDDy. Phase 2 will use this information to develop a customized mHealth app using an iterative model of software development. Phase 3 will involve a pre- and posttest design; the developed app will be tested among consenting patients, where physicians will receive the patients’ data through the HIS-integrated mHealth app. The pre- and posttest values will be analyzed for adherence leading to improvement in patients’ self-management of blood glucose, user experience, glycemic control, and clinical utility.

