## Methods

### Overview

The study will be carried out in the outpatient department (OPD) of the endocrinology department at a tertiary care hospital in a south Indian state, and it is divided into 3 phases. In phase 1, a qualitative study was conducted; in phase 2, the mobile app with be developed and integrated with a health information system (HIS); and finally, in phase 3, the developed app will be tested for its feasibility using a pre- and posttest design.

The study is based on the principles of the “theory of change,” where stakeholders will be consulted through in-depth interviews (IDIs) to identify the deterrents to acceptance and adherence of electronic diabetes-monitoring practices, potential challenges, as well as ethical issues related to electronic information sharing. This feedback will provide the cues for the development of a customized electronic diabetes-monitoring system. The study would also attempt to identify the reasons that would lead to the discontinuation of electronic monitoring practices among patient with T2DM and address them by developing a more user-friendly mHealth app. This study will also analyze the patient acceptance of the mHealth app and their adherence to SMBG practices.

The model will then be developed and integrated with an HIS. Finally, it will be tested among patients with T2DM regarding their acceptance and adherence to using the Electronic Diabetes Diary (EDDy), its usability, contextual relevance according to user expectation, and clinical utility in terms of glycemic control.

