#### Sample Selection

The IDI participants were enrolled according to the following criteria: patients who own an Android smartphone and those who regularly attend doctor’s appointments (ie, those who visit the OPD at least once in the last 6 months). Patients who are literate, can understand the local language (Kannada or Tulu) or English, aged 40-65 years, and have hemoglobin A_1c_ values between 7% and 10% were selected to ensure homogeneity. Patients with gestational diabetes and other terminal illnesses were excluded. The IDIs were conducted among the immediate caregivers of the patients (ie, those who are actively involved in the care of the patient). To understand the practical aspects of the treatment and management of patients, physicians, nurses, and counsellors were also interviewed.

Even with the availability of various diabetes management apps, studies suggest they are not very popular among the general population. The reason for this underuse and nonadherence, along with their expectations from mHealth apps, are the key areas that were addressed among patients with T2DM and their caregivers. The doctors and diabetes counselors were interviewed to understand the challenges they face while managing patients with T2DM and their SMBG practices.

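### Glycemic control is promised as a pre- and posttest evaluation, but its only definition describes monitoring behaviour and contains no glucose or HbA1c level

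*Protocol article*

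**What the plan says.** **What is promised.** The Abstract (Methods) states: "The pre- and posttest values will be analyzed for adherence leading to improvement in patients’ self-management of blood glucose, user experience, glycemic control, and clinical" (the quote stops one word before the end of the sentence, whose last item is clinical utility). The Overview, describing the final phase, says that the app will be tested for, among other things, "clinical utility in terms of glycemic control".

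**What is defined.** The phase 3 Analysis section says: "The participants will undergo an exit survey at the end of the study period using a validated questionnaire". It continues: "It will be specific for assessing the qualitative parameters such as" user experience, glycemic control, adherence and clinical utility. In the list of qualitative outcomes that follows, glycemic control is "Adherence in terms of regular monitoring and tracking of blood glucose values to keeps it under check", with well-managed T2DM named as the expected result.

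**Where HbA1c appears.** It is named only as an eligibility criterion, in Sample Selection for phase 1: patients with "values between 7% and 10% were selected to ensure homogeneity". Phase 3 adopts this: "The inclusion and exclusion criteria for sample collection will remain same as that of phase 1".

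**What the study is mainly about.** The second objective is "to evaluate and test adherence to EDDy in the management of T2DM". The sample size in the phase 3 Study Design section is set on adherence.

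**The concern.** The promise and the definition concern different things. A reader told that glycemic control improved between pretest and posttest will understand that glucose or HbA1c fell. Under the stated definition, the same sentence would mean that patients monitored and tracked their readings more regularly. A patient who faithfully records persistently high values meets the behavioural part of that definition.

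The definition also overlaps adherence, which is evaluated partly as entry of glucose values at the frequency the patient has chosen. The article expects better adherence to lead to better treatment outcomes (Expected Outcomes From EDDy). That expectation cannot be examined properly if the outcome on the far side of the link is itself described as adherence.

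This is not a detail deferred to an analysis plan. The article gives a definition, and an analysis that followed it faithfully would report behaviour under a glycemic label.

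**Working it through.** **Step 1: does any phase 3 measurement use a glucose or HbA1c level?**

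| Place in the article | What is collected | Is a level used as an outcome? |
|---|---|---|
| Study Design, first adherence component | Entry of glucose values at the frequency set by the patient; values stored in the app and sent to the server | No; the stated use is adherence of entry |
| Study Design, second and third components | Self-management practices by questionnaire; adherence to blood tests and comorbidity screening | No; whether tests are done, not their results |
| Study Design, first and third evaluations | The same questionnaire on self-management and glucose-monitoring practices | No |
| Analysis, exit survey | Qualitative parameters, glycemic control among them | No; defined as monitoring and tracking |
| Analysis, 12-item self-management tool | Self-care activities associated with glycemic control | No; the activities, not the control |
| Analysis, self-developed questionnaire | Regularity and ease of use, medication, reporting of complications, screening | No |
| Sample Selection | HbA1c of 7% to 10% | Eligibility only |

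No named outcome is built on a level. The raw material exists at least in part: an HbA1c value is needed for eligibility, and glucose readings accumulate on the server.

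**Step 2: is the primary analysis touched?** The inputs are in the phase 3 Study Design section: effect size f = 0.25, alpha 0.05, power 80%, m = 3 time points, correlation 0.3. Sphericity (epsilon = 1) is assumed because the article does not state it.

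- Noncentrality: lambda = f² × n × m / (1 − rho), with df1 = 2 and df2 = 2(n − 1).
- n = 37: lambda = 0.0625 × 37 × 3 / 0.7 = 9.91, power 0.794.
- n = 38: lambda = 0.0625 × 38 × 3 / 0.7 = 10.18, power 0.806.
- The minimum is therefore 38, as stated. Allowing for dropout, 38 / (1 − 0.20) = 47.5, rounded up to 48, as stated.

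This calculation concerns adherence only, and nothing in this point alters it.

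**Step 3: why the choice of baseline matters if HbA1c becomes an outcome.** This bears on the remedy. It does not measure the present defect. When patients are selected on a value between 7% and 10%, the expected drift of a later value is (1 − rho) × (mean within the selected range − clinic mean), under a normal distribution. The documents give none of these inputs, so all are assumptions:

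- clinic mean 7.5, SD 1.5, correlation 0.7: selected mean 8.215, so 0.3 × 0.715 = 0.21 points of apparent fall;
- clinic mean 8.0, SD 1.5, correlation 0.7: selected mean 8.355, so 0.3 × 0.355 = 0.11 points;
- over clinic means 7.0 to 8.0, SD 1.2 to 1.8 and correlation 0.6 to 0.8: about 0.06 to 0.48 points.

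The drift is zero at a clinic mean of 8.5, the midpoint of the range, and becomes an apparent rise above it. Both its direction and its size are therefore unknown here.

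**The case against.** The strongest reply is about scope. The formal objective, the sized outcome and the opening of the Analysis section all concern adherence, and the Overview describes phase 3 as a test of feasibility. Glycemic control is one item in a list. This stands, and it limits the severity: the trial's main question is not compromised.

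Three stronger readings are tempting, and the documents do not support them.

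- **That there is no pretest value.** A reader might infer this from the exit survey. But the third evaluation reuses the questionnaire from the first, and the article does not say whether the exit survey is separate from that evaluation. Its timing relative to the baseline questionnaire is ambiguous; absence of a baseline is not shown.
- **That the trial will yield no information at all on glycemia.** Glucose readings will be stored, the list is headed as the qualitative outcomes and is not said to be complete, the pre- and posttest figure is not shown, and a laboratory schedule may sit in the full protocol. What can be said is that the article names no outcome using a level.
- **That glycemic control and adherence are the same variable.** The definition mentions well-managed diabetes as a consequence, and no scoring rule is given. Overlap is supported; identity is not.

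It is also fair to object that the regression-to-the-mean range rests on assumed inputs and on an outcome the plan does not contain. It should not be read as the size of this problem.

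None of this reconciles the Abstract and Overview with the Analysis section. The definition given still measures behaviour.

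**Conclusion.** The point holds in a limited form, as something that should be fixed. The Abstract and Overview undertake to evaluate glycemic control within a pre- and posttest design; the Analysis section defines it as a qualitative, survey-based description of monitoring. As defined, it cannot support a statement that glycemic control changed.

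The consequence is confined to that secondary claim and to any inference that adherence improved glycemia. The defect is qualitative, so no numerical size attaches to it. The conclusion rests on the article's wording and assumes that the full protocol does not replace this definition with a measured one.

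**What to change.** 1. Rename the item in the Analysis section, for example as perceived control or monitoring behaviour, and keep it in the survey under that name.
2. Define glycemic control as a quantitative secondary outcome: change in HbA1c from baseline to about month 6 where routine results exist, reported as mean change with a 95% CI. Summarise app-stored glucose values by month as support.
3. Use a routine HbA1c from enrolment that is separate from the qualifying value, if one exists. Otherwise use the qualifying value and say so. Either way, state that the change cannot be attributed to EDDy: there is no control group, and patients were selected on 7% to 10%.
4. Report how many patients have HbA1c at both times and compare those with and without it. Adherence to routine blood tests is itself an outcome here, so missingness may be related to adherence.
5. If no glycemic measure will be analysed, remove the glycemic-control claim from the Abstract and the Overview instead.

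**Cost.** Items 1 and 5 are wording only. Items 2 to 4 need extraction of existing results and a short addition to the analysis. The article does not confirm that HbA1c is routinely measured at enrolment or month 6, so the number with paired values could fall short of the number enrolled, and the completers may be the more adherent patients. The choice is best made before phase 3 enrolment, because a baseline value not captured then may not be recoverable.
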